##### Training, monitoring and fidelity

3.6.2.1

On Day 0, a trained Co-Investigator will provide an in-person demonstration at the OPD to standardize oil quantity, application methods, and safety precautions. Participants or caregivers will receive illustrated bilingual pamphlets and video guides. *Ksirabala Taila*, sourced from the GMP-certified manufacturer, must be maintained at a lukewarm temperature prior to application. The designated investigator will verify participant competency during the session using a standardized procedural checklist. Adherence is monitored via Daily Sleep and Treatment Engagement Diary (DSTED) logs and weekly tele-supervision for 10% of the cohort to maintain intervention fidelity.

#### Cognitive Behavioral Therapy for Insomnia (intervention and control group)

3.6.3

Participants randomized to the control arm will receive Cognitive Behavioral Therapy for Insomnia (CBT-I) alone for 4 weeks. CBT-I will be delivered twice weekly in 45–60-min individual sessions, either in person or via telehealth, by trained and certified counseling psychologists with a minimum of 2 years of clinical experience. All CBT-I therapists will undergo a protocol orientation meeting prior to study initiation to ensure adherence to the standardized CBT-I manual used in this trial. Session content will be documented after each visit using structured therapist notes. Treatment will follow the same standardized CBT-I manual as described, including sleep restriction therapy, stimulus control therapy, cognitive restructuring, sleep hygiene education, and relapse prevention components.

Participants in the control arm will undergo the same follow-up schedule, outcome assessments, adherence monitoring procedures, and safety oversight as those in the intervention arm to ensure methodological parity between groups. A sham oleation procedure was not included, as standardizing a credible placebo tactile intervention was considered impractical in the context of this exploratory trial.

##### CBT-I module structure

3.6.3.1

A total of eight sessions follow a structured progression:

**Session 1:** Assessment, introduction to CBT-I, review of comorbidities, and instruction on sleep diary use.**Session 2:** Sleep Restriction Therapy (SRT) and Stimulus Control Therapy (SCT); introduction to the 3P Model of insomnia; setting the initial sleep prescription.**Session 3:** Sleep hygiene education, addressing barriers to adherence, reviewing sleep schedules.**Session 4:** Introduction to cognitive therapy principles and strategies.**Sessions 5–7:** Continued cognitive restructuring, adherence monitoring, adjustment of sleep prescription if sleep efficiency exceeds 90%, review of sleep hygiene.**Session 8:** Relapse prevention, review of progress, and final recommendations.

##### Educational guidance

3.6.3.2

All participants will be educated about the benefits of 7–9 h of sleep at night for a midlife adults and relevance of consistent sleep below 6 hours is considered insufficient. This information is for general education and does not affect outcome definitions.

### Intervention modifications

3.7

All missed sessions and protocol deviations will be documented in the participant’s CRF and reviewed during weekly study meetings.

Missed Ayurvedic Procedures.

Missed *Siro-pichu*: Not rescheduled later that night; documented as a protocol deviation; resume next scheduled session.Missed *Padabhyanga*: Resume at the next scheduled time; doubling sessions is not allowed.

Missed CBT-I Session.

May be rescheduled within the same week or delivered via telehealth within 48 h.

### Withdrawal criteria

3.8

Participants may be withdrawn from the study under the following circumstances:

Occurrence of a serious adverse event requiring urgent medical intervention.Initiation of pharmacological treatment for insomnia during the study period.Emergence of a psychiatric condition requiring immediate clinical management.Voluntary withdrawal of consent.

Symptom fluctuation or worsening insomnia severity alone will not constitute automatic withdrawal. Participants experiencing worsening symptoms will undergo clinical evaluation and supportive management. Non-compliance with the intervention schedule will be documented but will not automatically result in withdrawal. All randomized participants will be included in the intention-to-treat analysis wherever feasible.

Withdrawal decisions due to safety concerns will be made by the Principal Investigator in consultation with the Co-Investigator and documented in the CRF.

### Protocol adherence criteria

3.9

Adherence will be defined using quantitative thresholds to ensure objective assessment.

#### Adherence to Ayurvedic regimen

3.9.1

Adherence to *Siro-pichu* and *Padabhyanga* will be defined as completion of at least 80% of the prescribed applications during the intervention phase.Completion will be recorded in the Daily Sleep and Treatment Engagement Diary and reviewed during weekly follow-ups.Random tele-supervision (10% of participants) will be conducted to support procedural fidelity.

#### Adherence to CBT-I

3.9.2

Attendance requirement: participants will be considered adherent if they attend at least six sessions (75–80%) of the scheduled CBT sessions.Session documentation: attendance will be recorded by the therapist/facilitator after each session, and non-attendance will be followed up by reminder calls.Engagement in sessions: active participation (completion of exercises, discussions, and assignments) will also be documented to assess qualitative adherence.Make-up sessions: if participants miss a session, opportunities for catch-up or supplementary guidance will be offered, ensuring minimal loss of therapeutic continuity.

#### Adherence improving strategies

3.9.3

Daily DSTED diary entries.Weekly telephonic check-ins.Visual aids and instructional material for home practice.SMS/ WhatsApp reminders during the Ayurvedic regimen and prior to CBT-I sessions.Reinforcement during scheduled follow-up visits.

### Rescue medications

3.10

#### Mild to moderate symptoms

3.10.1

*Dhanwantharam Gulika* for mild headache.Steam inhalation and *Vyoshadi Vatakam* for nasal congestion.*Jeerakarishtam* for light-headedness.Coconut oil for mild local skin irritation.Warm water and light ambulation for drowsiness.Short nap (<30 min), sunlight exposure for daytime sleepiness.Breathing exercises and progressive muscle relaxation for irritability and stress.Motivational guidance for schedule adjustment difficulties.

#### Persistent or worsening symptoms

3.10.2

Referral to a modern medical practitioner.Non-pharmacological support measures.

#### Significant worsening of insomnia

3.10.3

Intervention paused.Referral to sleep specialist or psychiatrist.

All the rescue medications will be sourced from GMP certified manufacturers and the use of all such prescriptions will be documented in the CRF with date, indication, dosage and duration. Although these measures are intended to ensure participant safety and comfort, their use may introduce potential confounding effects on sleep related outcomes and will therefore be considered during interpretation of results.

## Outcome measures

4

All outcomes in this trial are exploratory in nature and are intended for estimation and hypothesis generation rather than confirmatory hypothesis testing.

### Exploratory primary outcome

4.1

(Assessed at Week 4—end of intervention phase).

Insomnia Severity Index (ISI) — change from baseline to Week 4.

Measurement variable: ISI total score (range 0–28).Analysis metric: Mean change from baseline to Week 4; between-group mean difference with 95% confidence interval.

### Exploratory secondary outcomes

4.2

The following outcomes explore early response, durability of effect, sleep quality, safety, behavioral reliance, and adherence. These analyses are exploratory and descriptive in nature. No adjustment for multiple comparisons is planned.

Pittsburgh Sleep Quality Index (PSQI) — change from baseline to Week 4.

Measurement variable: PSQI global score (range 0–21).Analysis metric: Mean change from baseline to Week 4; between-group mean difference with 95% confidence interval.

Early therapeutic response (ISI at Week 2).

Measurement variable: ISI total score at Week 2.Analysis metric: Between-group differences in mean change from baseline with 95% confidence intervals.

Durability of insomnia severity (ISI during follow-up).

Measurement variable: ISI total scores at Weeks 6, 8, 10, 12, 14, 16.Analysis metric: Mean change from baseline at each time point; descriptive summaries with between-group estimates.

Sleep quality during follow-up (PSQI).

Measurement variable: PSQI global scores at Weeks 8, 12, 16.Analysis metric: Mean change from baseline; descriptive between-group estimates.

Occurrence and characterization of clinically relevant events.

Measurement variable: Adverse events recorded using validated ADR/AE monitoring checklist (45, 46).Analysis metric: Frequency and proportion by group; descriptive summaries of severity and relatedness.

Behavioral dependency risk.

Measurement variable: Severity of Dependence Scale (SDS) total score (47), assessed through Week 16.Analysis metric: Mean change from baseline to Week 16; between-group estimates with 95% confidence intervals.

Treatment adherence and fidelity.

Measurement variable: Daily Sleep and Treatment Engagement Diary (DSTED) (48).Analysis metric: Percentage adherence and descriptive summaries.

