### Exploratory secondary objectives

2.2

To determine mean reduction in the Pittsburgh Sleep Quality Index (PSQI) score (42, 43) after 4 weeks of intervention with CBT-I added with external administration of *Siro-pichu* and *Padabhyanga* with *Ksirabala Taila*, compared to CBT-I alone.To determine the early onset of therapeutic response within the first 2 weeks of intervention using the ISI score, with a focus on changes in the severity of insomnia.To determine changes in insomnia severity during the three-month follow-up period, measured at two-week intervals using the ISI score.To determine the sleep quality measured using the PSQI score during the 3 months of follow up.To record the occurrence and severity of ADEs associated with the integrative protocol using a validated ADR monitoring checklist.To determine the potential psychological or behavioral dependency risk related to the adjunctive Ayurvedic therapies (*Siro-pichu* and *Padabhyanga*) using Severity of dependency Scale during the 3-month relapse prevention follow-up phase.To determine treatment adherence in both intervention and control groups using the Daily Sleep and Treatment Engagement Diary.

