### Participant timeline

4.3

Enrolled participants follow a sequence of screening, baseline intervention and follow up. During the initial screening (Week 0), the medical officer document demographic details, perimenopausal status (STRAW staging), and chronic insomnia symptoms which is occurring at least three nights per week for the past 3 months. Screening evaluations will include the Insomnia Severity Index (ISI) to determine eligibility, PHQ-9 to rule out depressive symptoms (≤5), review of recent medication use, and assessment of BMI (≤35). Baseline medical history, lifestyle factors (sleep schedule regularity, shift-work exclusion), and technology readiness (phone/internet access) will be verified. *Prakriti* (constitutional profile) assessment and documentation of baseline *Dosa dushti lakshaṇa* (etiopathogenesis with clinical presentation) related to *Nidranasa* (disturbance or loss of sleep) will be completed for descriptive and exploratory analysis. Written informed consent will be obtained at this stage. Following the screening visit, participants will attend a baseline assessment session, during which ISI, PSQI, sleep diary orientation, safety checks, completing the clinical evaluation. Screening and baseline visit may occur on the same day if eligibility is confirmed and consent is obtained. Following which a baseline evaluation is done and, participants are randomized into 1:1 groups. Participants in the add- on arm will receive *Siro-pichu* (7 days) and *Padabhyanga* twice daily (14 days) with demonstration, training and home based adherence monitoring, while both groups receive sleep hygiene education and eight twice-weekly sessions of CBT-I delivered by certified psychologists. Sessions will follow a structured CBT-I manual that includes sleep restriction, stimulus control, cognitive restructuring, relaxation training, and relapse-prevention modules. Adherence will be monitored through attendance logs, sleep diaries, DSTED entries, and telephonic check-ins. Upon completion of the intervention period (at Week 4), participants will attend an assessment post-intervention visit to repeat ISI, PSQI, and other outcome measures.

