#### Data collection procedures

4.8.1

Study data will be captured via standardized paper-based case record forms (CRFs) and validated outcome instruments. Trained research staff, independent of intervention delivery, will oversee data collection at the Outpatient Department (OPD) during screening and baseline. Subsequent intervention (Weeks 2, 4) and follow-up (Weeks 6–16) assessments will occur in person or via telehealth. Outcome instruments (ISI, PSQI, SDS, DSTED) are self-administered by participants under supervision of trained research staff independent of intervention delivery. Research staff may clarify instructions but will not influence responses (Table 1).

**Table 1 tab1:** Data collection methods.

Trial instrument	Purpose	Frequency of measurement	Timepoints of assessment
Insomnia Severity Index	To determine the primary outcome: severity of insomnia symptoms over the preceding two weeks	Every 2 weeks	Baseline (Week 0), Week 2, Week 4 (end of intervention), Week 6, Week 8, Week 12, Week 14, Week 16 (end of follow-up)
Pittsburgh Sleep Quality Index	To evaluate the overall sleep quality and its domains, including latency, duration, efficiency over the past month	Monthly	Baseline (Week 0), Post- treatment (Week 4), Follow-up Months 1, 2, and 3
ADR Monitoring Checklist	To identify and document any adverse events or reactions related to the integrative intervention	Ongoing monitoring at each contact point	Weekly during intervention (Weeks 0– 4), and monthly during follow-up (Months 1–3)
Severity of dependency Scale	To detect any signs of behavioral or psychological dependency on *Śiro-pichu* and *Pādābhyanga* therapies	Twice during the study	Post-intervention (Week 4), End of follow-up (week 16)
Daily Sleep and Treatment Engagement Diary	To assess adherence and consistency in following the prescribed intervention protocol	At the end of intervention and follow up	Week 4 of intervention, Week 16 of follow up

Official Malayalam versions of ISI and PSQI were obtained from ePROVIDE–MAPI Research Trust (COA request submitted 08-Aug-2025; approval date: 01 September 2025). Instruments will be administered in accordance with licensing terms. Table 1 shows the data collection methods in detail.

Sleep diaries will record total sleep time (TST). For descriptive summaries, TST will be categorized as optimal (7–9 h), short (<6 h), or long (>9 h). Classification is for characterization only and will not determine treatment response.

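### The SDS outcome is defined as a between-group change from baseline, but Table 1 schedules the SDS only at Weeks 4 and 16 and controls never receive the therapies it is meant to rate

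*Protocol article*

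**What the plan says.** **SDS, outcome definition.** Section 4.2 (Exploratory secondary outcomes) gives the variable as "Severity of Dependence Scale (SDS) total score (47), assessed through Week 16" and the analysis metric as "Mean change from baseline to Week 16; between-group estimates with 95% confidence intervals". Section 4.9.2 also has SDS scores compared between the arms with a parametric or non-parametric test.

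**SDS, schedule.** Table 1 (section 4.8.1) gives the frequency as "Twice during the study" and the time points as "Post-intervention (Week 4), End of follow-up (week 16"). Section 4.3 (Participant timeline) describes the baseline visit thus: "participants will attend a baseline assessment session, during which ISI, PSQI, sleep diary orientation, safety checks, completing the clinical evaluation". The SDS is not in that list.

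**SDS, construct.** The objective in section 2.2 is to determine the "potential psychological or behavioral dependency risk related to the adjunctive Ayurvedic therapies", and it places this in the three-month follow-up phase. The purpose column of Table 1 likewise ties the scale to Siro-pichu and Padabhyanga. Under sections 3.6.1 and 3.6.3 controls receive CBT-I alone, yet they undergo the same outcome assessments as the add-on arm.

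**ISI follow-up.** Section 4.2 analyses "ISI total scores at Weeks 6, 8, 10, 12, 14, 16". The time-point column of Table 1 ends with "Week 6, Week 8, Week 12, Week 14, Week 16 (end of follow-up"), without Week 10. The frequency column of the same row says the ISI is taken fortnightly, as does the objective in section 2.2.

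**The concern.** A change from baseline needs a baseline value, and the only schedule in the article does not provide one. The Week 4 value that is scheduled is not used by the metric. An analyst following section 4.2 would have to improvise, for example by substituting Week 4 for baseline, assuming zero at baseline, or comparing raw Week 16 scores. These are different quantities, and the choice would be made after the data are in.

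The second difficulty is one of meaning. Dependence on two oil procedures cannot sensibly be rated by a woman who has not had them. That applies to the add-on arm before Day 1 and to the control arm throughout. The between-group estimate therefore sets a rating of the therapies against answers whose subject is not defined.

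The SDS is the article's only measure of dependency risk, in a trial that lists safety among its aims. The outcome should be one that can be estimated and read.

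**Working it through.** **Figures used.** The article attaches no computed figure to the SDS. Its only calculation is the sample size for the ISI, used here just for the arm sizes. Section 4.5 gives SD 4.3, difference 4, two-sided alpha 0.05 and power 90%:

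- n = 2 × 4.3² × (1.960 + 1.282)² / 4² = 24.3, so 25 per group. The article says approximately 26.
- 26 / (1 − 0.15) = 30.6, so 31 per arm and 62 in total, as stated.

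The point below does not depend on this calculation.

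**Time points needed against time points scheduled.**

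| Instrument | Needed by section 4.2 (weeks) | Listed in Table 1 (weeks) | Needed, not listed | Listed, not used |
|---|---|---|---|---|
| SDS | 0, 16 | 4, 16 | 0 | 4 |
| ISI | 0, 2, 4, 6, 8, 10, 12, 14, 16 | 0, 2, 4, 6, 8, 12, 14, 16 | 10 | none |

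**Is the SDS gap a slip in the table?** In the SDS row the frequency (two) and the time points (Weeks 4 and 16) agree with each other. The ISI and PSQI rows of the same table do list baseline. Section 4.3 names ISI and PSQI at baseline and not the SDS. These signs point to a schedule that never included a baseline SDS, and to a metric in section 4.2 that was not matched to it.

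**Would adding a baseline help?** Let A₀ and A₁₆ be the add-on means at Weeks 0 and 16, and C₀ and C₁₆ the control means. The metric is (A₁₆ − A₀) − (C₁₆ − C₀).

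- If women without exposure score zero because there is nothing to rate, then A₀ = C₀ = C₁₆ = 0 and the metric reduces to A₁₆. With 31 per arm, add-on SD s and control SD 0, the pooled variance is (30s² + 0)/60 = s²/2. The standard error is √(s²/2 × 2/31) = s/√31, the same as for the add-on mean alone. The comparison then adds nothing.
- If women without exposure answer about something else, such as CBT-I or sleep habits, the metric subtracts a different construct and has no clear interpretation.
- If they leave the form blank, there is no comparison.

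The article does not say which would occur, and in none of the three cases does the between-group estimate add information about dependence on the therapies.

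**What the schedule does support.** Padabhyanga ends on Day 14 and Siro-pichu on Day 7, so both SDS assessments fall after exposure has ended. Weeks 4 to 16 span 16 − 4 = 12 weeks, which is the follow-up phase named in the objective. SDS totals at those two visits, and the change between them in the add-on arm, are computable and answer the stated objective.

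**ISI at Week 10.** A fortnightly schedule over Weeks 0 to 16 has 9 time points and Table 1 lists 8. Section 4.2, the objective in 2.2 and the frequency entry in the same table row all include Week 10. Only the time-point cell leaves it out.

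**The case against.** The strongest reply concerns weight. Section 4.2 calls these analyses exploratory and descriptive. The Limitations section concedes that the SDS is a behavioral proxy, not validated for non-pharmacological procedures, and to be read with caution. The primary outcome (ISI change to Week 4), its analysis and the sample size do not touch the SDS. This lowers the severity, and that part stands. It does not remove the defect: the stated limitation concerns validity of the scale and mentions neither the absent baseline nor the unexposed comparator. An exploratory estimate still has to be computable.

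Several stronger readings are tempting and go beyond the text.

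- A reader might infer that no woman will have a baseline SDS. Section 4.2 presupposes one, and section 4.3 says the Week 4 visit repeats ISI, PSQI and further outcome measures, which could hint at earlier administration. Table 1 is the likelier guide, but what the documents establish is a contradiction to be reconciled.
- A reader might infer that the comparison makes the add-on arm look worse by construction. The adapted SDS wording and its scoring in controls are not shown. If controls score zero, the difference is simply the add-on arm's own level, which is redundant but not biased.
- A reader might infer that every participant will lack a Week 10 ISI. Three statements include that assessment and one cell omits it, so an omission from the table is the better explanation.

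A further fair objection is to withholding the form from controls. Section 4.7.3 has a blinded assessor administer the follow-up measures, and Week 4 is the primary-outcome visit. A form handed to one arm only could reveal allocation there. It would also contradict the parity of assessments promised in section 3.6.3. This stands, and the fix must allow for it.

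**Conclusion.** The point holds. The SDS metric in section 4.2 and the SDS schedule in Table 1 disagree, nothing else in the article resolves the disagreement, and the outcome cannot be computed as written. Given the construct stated in section 2.2 and Table 1, a pre-exposure baseline and a comparison with the 31 planned controls have no clear meaning either, so adding a baseline assessment is not a remedy.

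The size is one exploratory secondary outcome, of moderate severity. The missing Week 10 entry in the ISI row is a separate, minor table correction. The primary outcome, its analysis and the sample size are unaffected.

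This rests on two assumptions: that Table 1 is the operative SDS schedule, and that the SDS items refer to the two procedures, as the objective and the table's purpose column say. If the items given to controls refer to something else, the article needs to state what that is.

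**What to change.** 1. In section 4.2, redefine the SDS outcome as the total score at Week 4 and at Week 16, and the within-arm change from Week 4 to Week 16 with a 95% confidence interval, in the add-on arm. Delete the change from baseline and the between-group estimate.
2. In section 4.9.2, delete the between-group SDS test and leave the descriptive summary for the add-on arm.
3. State who completes the form, by one of two routes:
   - *Both arms.* Keep administration as now and state that control scores are not analysed as dependence on the therapies. This leaves blinding and section 3.6.3 untouched.
   - *Add-on arm only.* Have already unblinded staff handle the form, away from the blinded assessor, and amend the statement in section 3.6.3 that controls undergo the same outcome assessments. Sections 4.7.3.2 and 4.8.1 would also need a short exception. The first keeps the Medical Officer out of outcome assessment, and the second requires supervising staff to be independent of intervention delivery.
4. In Table 1, add Week 10 to the ISI time points.

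The cost is wording in sections 4.2 and 4.9.2 and one table cell, plus the amendments above if the second route is chosen. No SDS assessment is added, and the Week 10 ISI is already implied by the fortnightly schedule.
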